## Abstract

**Background:**

Percutaneous coronary intervention (PCI) is widely used in China, but it does not fundamentally improve exercise endurance or reduce mortality associated with cardiovascular disease. Standardized cardiac rehabilitation (CR) can reduce the mortality associated with coronary heart disease and reduce the need for repeated PCI procedures. Currently, research on CR after PCI is mainly based on traditional exercise prescription, while research on TCM is limited. Often, the combination of traditional Chinese medicine (TCM) and exercise rehabilitation is adopted, from which it is difficult to determine the unique advantages of TCM. Qishen Yiqi dripping pills (QSYQ) can improve myocardial energy metabolism and alleviate myocardial reperfusion injury after PCI. This paper describes the protocol for the clinical assessment of QSYQ on CR.

**Methods:**

A randomized, double-blind, placebo-controlled trial will be used to evaluate the efficacy and safety of QSYQ on improving exercise endurance and quality of life. We plan to recruit 66 patients with stable angina pectoris with Qi deficiency and blood stasis syndrome differentiation after PCI from the China-Japan Friendship Hospital. On the basis of conventional drug treatment, QSYQ or placebo will be used for 12 weeks. PeakVO_2_ will be the main efficacy evaluation index, while Seattle scale and quality of life scale will be the secondary efficacy evaluation indexes. *Discussion*. CR therapy with integrated traditional Chinese and Western medicine has been developed as a treatment modality in China and has been included in the expert consensus of TCM diagnosis and treatment. A rigorous trial design will ensure objective and scientific evaluation of the efficacy and safety of QSYQ in improving exercise endurance and quality of life in patients with PCI. *Trial Registration*. This trial is registered with Clinical trial registration in China: ChiCTR2000040838 (registration date: December 11, 2020).

## 1. Introduction

Percutaneous coronary intervention (PCI) is the most important revascularization method for patients with coronary heart disease and is widely used in clinical practice [1]. However, several issues remain, including decreased exercise endurance and decreased quality of life. Moreover, despite rigorous pharmacological interventions in patients after PCI [2], the recurrence rate of cardiovascular events is as high as 34%. Therefore, the importance of effective cardiac rehabilitation (CR) of patients after PCI cannot be ignored. Previous studies in China [3, 4] have shown that CR can effectively reduce the total mortality rate, cardiovascular mortality rate, and rehospitalization and improve the quality of life. Integrated Chinese and Western medicine treatment after PCI is a common and effective CR mode [5].

According to traditional Chinese medicine (TCM), “blood stasis syndrome” is the most common cause of coronary heart disease angina pectoris and occurs throughout the development of coronary heart disease [6]. According to the research of [name] team, “Qi deficiency and blood stasis” belong to “original deficiency and standard solid” and are the core pathogenesis of reperfusion injury, myocardial hypertrophy, and chronic heart failure after interventional surgery [7]. Although interventional surgery can improve the blood supply to the heart, it does not change the “standard” and cannot improve the overall state of “blood stasis.” Additionally, from the perspective of TCM, interventional surgery belongs to mechanical and exogenous injury, which can destroy Healthy Qi and cause damage to the veins [8]. According to the theory of TCM, Qi and blood run through the pulse. If Qi is insufficient, it will affect the blood circulation and lead to blood stasis. Blood stasis will also affect the generation of Qi, leading to Qi deficiency. Qi deficiency and blood stasis interact, making the condition complex. This situation complicates the pathogenesis and increases the severity of the condition.

Qishen Yiqi dripping pills (QSYQ) were approved by the China Food and Drug Administration in 2003 for treating angina pectoris of coronary heart disease (approval number: YBZ04332003-2008Z). QSYQ is a TCM preparation developed by Tasly Pharmaceutical Group Co., Ltd., which functions to invigorate Qi, relieve pain, and promote blood circulation. The pills are composed of *Astragalus membranaceus*, *Salvia miltiorrhiza*, Panax notoginseng, and Dalbergia odorifera oil. Astragaloside IV inhibits abnormal energy metabolism pathways; Danshensu inhibits oxidative stress injury; notoginseng R1 partially improves myocardial energy metabolism and inhibits oxidative stress injury; and *Dalbergia odorifera* oil upregulates CPT1A. Multitarget comprehensive intervention in the above four components improves myocardial injury and inhibits myocardial fibrosis [7]. A large multicenter clinical study showed that Qishen Yiqi dripping pills had clinical efficacy in the secondary prevention of coronary heart disease [9]. Moreover, experimental studies [10] showed that QSYQ could effectively reduce the damage to myocardial cells caused by ischemia reperfusion and protect the myocardium. Studies have also found [11] that QSYQ can effectively improve the level of serum inflammatory factors in patients after PCI, increase left ventricular ejection fraction (LVEF) and cardiac output, reduce the volume at the end of the contraction and diastolic period, and reduce the recurrence of cardiovascular events.

At present, the combination of TCM and exercise prescription is often adopted, in which it is difficult to determine the unique advantages of TCM. However, there are few studies on TCM alone. Additionally, the evaluation of sports endurance rarely uses the gold standard, such as peak oxygen consumption (PeakVO_2_) and anaerobic metabolic threshold oxygen consumption (VO_2_AT) [12, 13]. Particularly, no clinical study of TCM compounds using the combination of disease and syndrome and randomized double-blind placebo control has yet been performed.

Therefore, we designed a randomized, double-blind, placebo-controlled clinical trial to evaluate the effects of QSYQ on exercise endurance and quality of life in patients with coronary heart disease after interventional surgery. To this end, we used the peak oxygen consumption in a cardiopulmonary exercise trial as the main efficacy evaluation.

## 2. Methods/Design

### 2.1. Objectives

The application of Qishen Yiqi dripping pills can improve the exercise endurance of patients with coronary heart disease after interventional therapy, improve cardiac function, reduce recurrence of angina pectoris, and improve the quality of life of patients.

### 2.2. Design and Settings

This trial is a randomized, double-blind, placebo-controlled clinical study, with 66 subjects planned to be enrolled. Informed consent will be signed after patients are screened by inclusion and exclusion criteria. The researchers will randomly divide the subjects into the QSYQ group and the blank placebo control group according to the time of enrollment. Before enrollment, there will be a 1-week screening period, during which other TCM drugs for CHD will be stopped. After entering the group, the patients will receive 12 weeks of medication. The flowchart of the research process is shown in Figure 1. All subjects will be followed up every 2 weeks after enrollment and will be monitored and evaluated at each follow-up. The technology roadmap is shown in Figure 2.

### 2.3. Participant Recruitment

The subjects will be recruited both on and offline. Patients who are interested in participating will decide whether to participate after being informed of the study content and purpose. The patients will be screened by the researcher according to the inclusion and exclusion criteria. Patients with “definite diagnosis of coronary heart disease,” “successful completion of interventional therapy,” and “syndrome differentiation of Qi deficiency and blood stasis after interventional therapy” will be allowed to participate.

### 2.4. Study Population

#### 2.4.1. Diagnostic Criteria

The criteria for successful intervention are as follows [14]: (1) successful angiography, in which the lumen of the coronary artery target site is significantly enlarged, with residual stenosis <50%, and achievement of TIMI-level 3 blood flow; (2) successful operation, in which the standard of successful angiography was achieved, with no major clinical complications (such as death, myocardial infarction, and emergency coronary artery bypass grafting) during hospitalization.

Diagnostic criteria of Western medicine: diagnostic criteria were devised by referring to the 2007 Guidelines for the Diagnosis and Treatment of Chronic Stable Angina Pectoris [15] and the 2016 Guidelines for the Diagnosis and Treatment of Non-ST Segment Elevation Acute Coronary Syndromes [16].

Diagnostic criteria of Qi deficiency and blood stasis syndrome: the criteria were formulated according to the Study on Syndrome Differentiation Criteria of Coronary Heart Disease after Vascular Reconstruction [17], as shown in Table 1.

#### 2.4.2. Inclusion Criteria

Inclusion criteria were as follows:Patients with a clear understanding of the content and purpose of the study, who will participate in the study voluntarily, and sign the informed consentConformed to the diagnostic criteria of Western medicine for stable coronary heart diseasePatients with Qi deficiency and blood stasis syndrome who meet the abovementioned TCM diagnostic criteriaComplete the overall treatment plan after PCIPostcoronary heart disease intervention (1–6 months)Age 18–75 yearsPostcoronary heart disease intervention (1–6 months)

#### 2.4.3. Exclusion Criteria

Exclusion criteria were as follows:Contraindications to cardiopulmonary exercise testPlanned coronary artery bypass grafting or heart transplantStroke or transient ischemic attack occurred within 3 months before enrollment; carotid or other large vessel surgery; persistent ventricular tachycardia or ventricular fibrillationVentricular arrhythmia not effectively controlled with use of antiarrhythmic drugs or implanted defibrillatorsUncorrected primary obstructive or severe reflux valvular disease, or nondilated (restrictive) or hypertrophic cardiomyopathySecond- or third-degree heart block or pathological sinoatrial syndrome, without permanent pacemaker, and patients who require implantable device treatment due to heart failureObstructive or bronchospasmodic lung disease (such as asthma or bronchitis) requiring oral or inhaled bronchodilators or hormone treatmentFemales who are pregnant or lactating, or who plan to become pregnant during the trialCancer or other systemic disease with an expected survival of <12 monthsUse of other clinical trial drugs or have participated in medical device trials in the 30 days prior to enrollmentDeemed unable to participate in the study after clinical evaluation

#### 2.4.4. Shedding and Selection Criteria

Shedding and Selection criteria were as follows:No index of peak oxygen consumption during cardiopulmonary exercise was obtained at the end of the experimentIf a serious adverse event occurs, the researcher determines that it is necessary to withdraw the patient from the trial in advanceDrug treatment compliance during maintenance period <80%The treatment process of the subjects seriously deviated from the study protocol

### 2.5. Randomization, Allocation Concealment Mechanism, and Blinding

#### 2.5.1. Random Allocation

Randomization of subjects: studies have shown that the number of diseased vessels and complicated lesions (hypertension, diabetes, and other chronic diseases) are independent risk factors affecting the recurrence of cardiovascular events after PCI and significantly influence prognosis [18]. To reduce selection bias and balance various non-study factors between groups, two factors affecting the prognosis of interventional surgery were set in this study [19–21]: (1) sex, male or female and (2) number of diseased vessels, single-, double-, or multiple-branch lesions. An online dynamic random method will be used to design and allocate hiding. Subjects will be randomly divided into the QSYQ group and the placebo group at a 1 : 1 ratio. We plan to use the clinical trial data management platform commissioned by the China-Japan Friendship Hospital to generate the random number and group number with the “YinRuiDa Randomization and Drug Management System.” Following provision of informed consent, the patient's name and ID number will be input into the “YinRuiDa Randomization and Drug Management System,” and a random number and group number will be generated. The patient number for each subject will remain the same throughout the study.

Drug random grouping: each patient will receive the drug or placebo 3 times, every 28 days (*n* = 99 copies per group; 1 copy = 1 dose for 28 days per person). SAS version 9.4 statistical software will be used to generate numbers 1–198, with each dose for 28 days per person being allocated one number.

#### 2.5.2. Blinding

The clinical trial data management platform of the China-Japan Friendship Hospital will be entrusted as the third party, and the “YinRuiDa Randomization and Drug Management System” will be used for grouping. Neither the subjects nor researchers will know the specific grouping results. To keep the study double-blind, QSYQ and placebo will be packaged in the same way, and the pills will be identical in shape, color, odor, and weight. Drug coding blindness takes one dose for 28 days per person as the unit, and each patient will be given drugs three times. Each drug will have a serial number, and the drug information hidden in each serial number will be entrusted to the third party for online storage.

#### 2.5.3. Unblinding

The first blinding will be performed after treatment; that is, all of the patients will be divided into groups A and B. After the end of the experiment, the blinding will be broken for the second time; that is, the blinding will be broken for group A or group B (QSYQ group or placebo control group). If serious adverse events (AES) occur, the results will be unblinded twice in two steps.

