### 3.2. Data Management

In this study, case report form (CRF) tables will be used to collect data. The subject information will not be directly recorded in the CRF but will be recorded on the original medical record of each subject, which will be retained as the original data. Medical and other records of subjects will be maintained by the investigator. These records should include the following: original data, copies of laboratory data, and results of other medical tests (e.g., electrocardiogram, etc.). The data in the CRF table will be taken from the original medical records and filled in by the researcher or the person designated by the researcher. The completeness and accuracy of the information will be ensured. The name of the person who made the change and the date of the change will be immediately recorded for any changes made to the CRF table. Upon completion of the CRF, it shall be submitted to the Data Statistics Center of the China-Japan Friendship Hospital in time for confirmation following raw data verification (SDV), data manager (DM) review, questioning, and other processing. Before data locking, the researcher will confirm the completeness and accuracy of data by signature. This trial has been registered in the “China Clinical Trial Registry” (http://www.chictr.org.cn/index.aspx) before the formal start of the trial. To facilitate follow-up tracing and verify the authenticity of the data, the study data related to the trial will be uploaded to the above website and made public at the end of the trial. The registration number is ChiCTR2000040838 (registration date is December 11, 2020).

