### 3.4. Quality Control

Before the start of the clinical trial, all investigators in the clinical study will participate in Good Clinical Practice (GCP) training, including the GCP regulations and standard operating procedures. All investigators are trained in research protocols and procedures, will read and understand the content of the clinical study protocol, master the principles of GCP, unify the recording methods and judgment standards, and strictly follow the protocol. All participants in the test will have clear responsibilities, act according to the rules, and assume their own responsibilities.

After completing the CRF, it will be submitted to the data statistics center in time for data verification and data locking. Data verification will include manual verification and data verification meetings. The researcher or the personnel designated by the researcher shall correct any inconsistent data found in the verification. Following confirmation that the CRF data are correct at the verification meeting, the main investigator, sponsor, and statistical analyst will sign the relevant documents to lock the test data. The locked data are not allowed to be changed in principle. Data problems discovered after a data lock will be confirmed for revision and documented in accordance with the provisions of the data management plan.

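### Section 2.5.3 applies the two trial-wide unblinding steps when a serious adverse event occurs, so as written one event could unblind all 66 patients; the A/B split is also not tied to database lock

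*Protocol article*

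**What the plan says.** Section 2.5.2 (Blinding) sets the standard: "Neither the subjects nor researchers will know the specific grouping results". Treatment codes sit outside the research team: "the drug information hidden in each serial number will be entrusted to the third party for online storage".

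Section 2.5.3 (Unblinding) sets out two steps.

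- Step 1: "The first blinding will be performed after treatment; that is, all of the patients will be divided into groups A and B". From the context, unblinding is meant.
- Step 2: "After the end of the experiment, the blinding will be broken for the second time". The letters are then identified as QSYQ or placebo.

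The section closes with the SAE rule: "If serious adverse events (AES) occur, the results will be unblinded twice in two steps".

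Section 3.1 requires an SAE form and a report to the Ethics Committee within 24 hours, and does not mention the treatment code.

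Sections 3.2 and 3.4 describe source verification, queries, a verification meeting and lock. Section 3.2 says: "Before data locking, the researcher will confirm the completeness and accuracy of data by signature". Section 3.4 says that after the meeting "the main investigator, sponsor, and statistical analyst will sign the relevant documents to lock the test data". Neither section mentions the A/B split.

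**The concern.** An SAE normally calls, at most, for disclosing one participant's treatment to those who need it. The only two steps that section 2.5.3 defines act on the whole trial, and the SAE sentence invokes two steps without naming a participant. Someone following the text would open the group code for everyone.

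If that happened while patients were still being treated and assessed, the main outcomes would be vulnerable. Peak VO2 depends on the effort the patient makes and on how the test is conducted. The TCM symptom table, the Seattle scale and the quality-of-life scale are reported or rated subjectively. Known allocation can shift all of these, and the placebo control would no longer protect the comparison.

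A smaller concern is timing. Step 1 is fixed by the end of treatment and not by database lock. Section 2.4.4 includes a removal criterion that needs judgement, serious deviation from the protocol. If A/B labels were available when such cases were decided, the decisions could differ by group.

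**Working it through.** **The SAE clause, sections side by side**

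1. Scope of the steps. In 2.5.3, step 1 covers all patients and step 2 identifies the groups. The article defines no other unblinding step.
2. Trigger. The SAE sentence calls for unblinding in two steps. With only two steps defined, the plain reading is that both are carried out.
3. Limit. Neither 2.5.3 nor 3.1 restricts the break to the affected participant.
4. Conflict. 2.5.2 keeps subjects and researchers blind. A group-level break after one event would end that for everyone.
5. One-patient reading. Suppose the two steps apply only to the affected patient. They reveal that this patient is in, say, group A, and then what A is. The second fact is the key for the whole trial. From the moment the A/B list is released after treatment, every allocation can be decoded, ahead of the planned second break. This reading avoids immediate trial-wide unblinding but still gives away the group key.
6. No need for the group key. Section 2.5.1 numbers each 28-day pack separately: 66 patients × 3 packs = 198 numbers, 99 per group. Section 2.5.2 has a third party store the drug information for each serial number. One patient's treatment could be read from a pack number without opening A or B.

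**How often the clause might be triggered**

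The article states no SAE rate, so there is no figure of its own to reproduce. Inputs: N = 66 (section 2.2; 2 × 33 in 2.5.4) and an assumed 12-week SAE risk p per patient, taken as independent between patients.

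P(at least one SAE) = 1 − (1 − p)^66

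| Assumed p | (1 − p)^66 | P(at least one) |
|---|---|---|
| 0.5% | 0.718 | 28% |
| 1% | 0.515 | 48% |
| 2% | 0.264 | 74% |
| 3% | 0.134 | 87% |
| 5% | 0.034 | 97% |
| 10% | 0.001 | 99.9% |

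These figures say how often an SAE might occur. They are not the probability that the trial is unblinded, which depends on how the sentence is applied.

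**Timing of the A/B split**

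1. 2.5.3 places step 1 after treatment and step 2 after the end of the experiment.
2. 3.2 and 3.4 place verification, queries and corrections before lock.
3. No section says whether step 1 comes before or after lock, or who receives the split. Release before lock is therefore allowed, but not stated.
4. Of the four criteria in 2.4.4, missing peak VO2 and compliance below 80% are factual. Withdrawal after an SAE is a judgement made during the trial. Serious deviation from the protocol is the one that could plausibly be judged at data review.

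**The case against.** The SAE sentence is poorly worded, and so is the text before it, which speaks of blinding where unblinding is meant. The authors may have intended a two-step break for the affected patient only, and the third-party storage by serial number would support that. A condensed article may also leave emergency procedures to the full protocol. Part of this stands: the article does not clearly announce a plan to unblind everyone, and the absence of a detailed code-break procedure is no fault in itself. The finding rests on a rule that is stated. Its plain reading is trial-wide, and even the one-patient reading exposes the group key.

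Two stronger readings are tempting and should be resisted. A reader might infer that group labels will be in view throughout data cleaning. The text does not say so: release after treatment is compatible with release after lock, the recipients are not named, and section 3.4 refers to a data management plan that is not shown. The effort and rating argument does not carry over to this point either. A split made after treatment follows the treatment-period assessments, and the letters alone do not identify QSYQ.

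A reader might also take the 34% recurrence of cardiovascular events in the Introduction as a guide to the SAE risk. It is background, has no time frame and is not a 12-week SAE rate.

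**Conclusion.** The SAE clause needs correction. Section 2.5.3 as written permits one SAE to unblind all 66 patients, contrary to 2.5.2, and places no limit to the participant concerned. If this happened during the trial, the primary outcome and the symptom and quality-of-life scales would be at risk of bias. The size of that bias cannot be derived from the article. The chance that the clause is triggered at all is about 48% to 97% for assumed per-patient risks of 1% to 5%; those risks are assumptions.

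The timing point is secondary and conditional. Labels could be available while queries and serious-deviation exclusions are settled, because the A/B split is not tied to lock. The documents do not show that they will be.

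**What to change.** Reword section 2.5.3 and reconcile it with 2.5.2:

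1. Any code break for an SAE concerns that participant only. It goes through the third-party system, is logged, is disclosed only to those who need it, and leaves the group codes closed.
2. The A/B split is released only after the analysis sets are fixed and the database is locked. Sections 3.2 and 3.4 should say the same.
3. A and B are identified only after the primary analysis by A/B is complete.

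The cost is a wording change plus access control for individual code breaks in a system that already stores drug information by serial number. No extra patients or staff should be needed. Section 3.5 says recruitment was under way, so the amendment should also record whether the present clause has been used.
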